##### Burnout

Burnout is measured with a slightly adjusted, Dutch version of the Maslach Burnout Inventory-General Survey (MBI-GS) [70], named Utrecht Burnout Scale (UBOS) [71]. This 16-item questionnaire includes the key dimensions of burnout: emotional exhaustion (feeling drained by the work), depersonalization (a cynical attitude towards the work and people working with) and reduced personal accomplishment (feeling incompetent at work). Response scales range from 0 = *never* to 6 = *every day*. Several studies have shown that the MBI-GS and its subscales are excellently reliable and valid (e.g. [72,73]).

##### Inrole performance and knowledge and skills

Inrole performance is considered the achievement of work-related goals and measured by three items of the Netherlands Working Conditions Survey 2010 [62], with a response scale ranging from 1 = *strongly disagree* to 5 = *strongly agree*. Furthermore, the fit between current knowledge, skills and job tasks is measured by asking one item from NWCS 2011 [3]: “How do your knowledge and skills fit your current work?”. Response scales range from 1 = *less knowledge and skills than needed*, to 2 = *it fits* to 3 = *more knowledge and skills than needed*.

##### Willingness and ability to prolong working life

The willingness and ability to prolong working life is measured by asking two open ended items from the Netherlands Working Conditions Survey 2010 [62]: Until what age do you (1) think you are able to continue working, and (2) want to continue working?

##### Productivity

Individual productivity in work is measured by a single item, based on module E of the PRODIDSQ [74]. PRODISQ is a scale considered to facilitate the validity of productivity costs estimates [75]. This single item measures self-rated productivity (“How would you assess your overall work performance in the past 4 weeks on a scale of 0 to 10?”) from 0 = *worst quality* to 10 = *best quality*.

### Measuring instruments: mediating factors

#### Occupational self-efficacy

Occupational self-efficacy is described as the confidence a worker has in his or her perceived ability to perform job tasks successfully [76]. The short (6 item) version of the Occupational Self-efficacy scale [77] measures the concept in a valid and reliable way (alpha 0.85) on a five-point Likert scale from 1 = *totally disagree* to 5 = *totally agree*[76].

#### Organizational efficacy

Organizational efficacy is defined as ‘an individual’s perception of the general capabilities of an organization’ ([78], p. 127). Van Vuuren’s seven item Organizational Efficacy Scale (OES) [78] has shown to measure the concept reliably (alpha 0.81) on a five-point Likert scale (1 = *strongly disagree*, 5 = *strongly agree*).

### Measuring instruments: sociodemographic and profiling data

Sociodemographic data are collected at baseline, i.e.: gender; age; level of education; household composition; working hours per week; number of years working in current function, school and sector; main workplace location.

Profiling data are collected either at baseline or at follow-up measurements for a practical reason. A practical reason is that response rates would drop if questionnaires would be too intrusive. Profiling questions are considered stable over time, which makes the measurement moment less important.

#### Locus of Control

Locus of control is considered a personality trait and defined as the extent to which people believe they can influence the course of their lives [79]. The construct comprises two dimensions - internal and external locus of control - and can be measured with 8 items on a seven-point Likert-scale (1 = *totally disagree* to 7 = *totally agree*) [80]. The subscale internal locus of control has shown poor reliability (alpha 0.43) and the subscale external locus of control has shown moderate reliability (alpha 0.66) in a German population of youngsters [80]. The replication of the theoretical two factor structure in an exploratory factor analysis, indicates that the instrument’s validity might be more promising [80]. Despite the problematic reliability, the Nolte-scale was preferred over the original I-E scale by Rotter (23 items) [79], because it is more compact. The Nolte-scale is translated to Dutch by a native German speaker living in The Netherlands for long and then back-translated to German by a native Dutch speaker living in Germany for long.

#### Parent and pupil (mis)behavior

The extent to which employees are bothered by (mis)behavior of pupils and parents in their work, is measured by a Dutch scale designed for the (primary) educational sector, named Welzijnscheck Onderwijspersoneel [57]. Misbehavior of pupils is measured reliably (alpha 0.82) with six items on a six-point scale ranging from 1 = *not applicable* to 6 = *in a very great degree*) [58]. On the same six-point scale, misbehavior of parents is measured reliably (alpha 0.78) with four items [58].

#### Work-life interference

Work-life interference is measured by one explorative item (“Does your work interfere with your private life?”) as well as life-work interference (“Does your private life interfere with your work?”), on a five point Likert scale ranging from 1 = *almost never* to 5 = *almost always*.

#### Institutional policy and educational quality

Workers’ knowledge of institutional policies is measured by one explorative item (“I am aware of the policies of my organization”) on a five-point Likert scale ranging from 1 = *strongly disagree* to 5 = *strongly agree*. The workers’ perception of the educational quality is also measured by one explorative item (“Our school prepares participants well for professional practice”) on a five-point Likert scale ranging from 1 = *strongly disagree* to 5 = *strongly agree*.

### Data analysis

#### Effect evaluation

The effectiveness of the intervention on primary outcomes (need for recovery and vitality) and secondary outcomes at short term (T1), long term (T2) and corrected for baseline values, will be established by multilevel analyses. Repeated measurements on the worker-level and clustering of observations can thus be taken into account. The data will be analyzed at three levels: 1) worker, 2) department, and 3) school. Both crude and adjusted linear and logistic regression analyses will be conducted. The intention-to-treat principle is leading in all statistical analyses, meaning that the analyses are based on the initial treatment assignment and not on the treatment eventually received. However, per-protocol analysis will also be conducted, restricting the comparison to the ideal participants, in this study: participants that report taking part in at least two of the three steps of the needs assessment.

Multilevel analyses wherein T1 functions as the dependent variable, will be adjusted for possible confounding factors (e.g. experience, overtime). These variables will also be checked for effect modification at all measurement moments.

For all analyses, a two-tailed significance level of p < 0.05 will be considered statistically significant. The multilevel analyses will be conducted by means of MlwiN 2.0; linear and logistic regression analyses will be performed using SPSS 17.0 (SPSS Inc. Chicago, Illinois, USA).

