### Study objectives

The current study tests a participatory, primary preventive organizational level intervention (i.e. a participatory action approach) that targets and engages all workers in the primary process of schools. Participation of employees and managers is supposed to result in increased occupational self-efficacy and organizational efficacy. The application of the intervention will yield work-oriented solutions tailored to the school setting, changing (the balance between) specific job demands and job resources. By improving the balance between job demands and job resources, it is expected to improve precursors of burnout (i.e. high need for recovery, low vitality) in the long run. The central research question is thus: is an organization focused stress management intervention based on participatory action effective in reducing the need for recovery and enhancing vitality in school employees in comparison to business as usual?

In this article we present the design of a controlled trial in two vocational schools in the Netherlands, wherein the participatory action approach and resulting work-oriented solutions are tested empirically.

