#### Study population

The intervention is applied to one department in both schools, another department in the same school is matched by the researchers as a control group. The target group of the project are teaching and non-teaching (i.e. educational and administrative support staff) employees in two vocational education institutions and their managers. Employees who work within the vocational institution, but do not teach at a secondary vocational level are excluded from the study population (e.g. teachers in general secondary education for adults). All participants are asked to sign an informed consent at baseline.

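### With only four departments, the multilevel test of the arm effect at p < 0.05 rests on about one degree of freedom and is anti-conservative if departments differ even slightly

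*Protocol article*

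**What the plan says.** Under Effect evaluation, the protocol article says that effects on need for recovery, vitality and the secondary outcomes, "at short term (T1), long term (T2) and corrected for baseline values, will be established by multilevel analyses". It continues: "Repeated measurements on the worker-level and clustering of observations can thus be taken into account", and then: "The data will be analyzed at three levels: 1) worker, 2) department, and 3) school". The decision rule is: "For all analyses, a two-tailed significance level of p < 0.05 will be considered statistically significant". The multilevel models are assigned to MLwiN. Separately, "linear and logistic regression analyses will be performed using SPSS 17.0".

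The number of units is fixed elsewhere. Study objectives describes "the design of a controlled trial in two vocational schools in the Netherlands". Study population says: "The intervention is applied to one department in both schools, another department in the same school is matched". That gives two units at the school level and four at the department level, two per arm. The article states no ICC, design effect or small-sample correction.

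**The concern.** The intervention is given to whole departments, so its effect is a contrast between departments. However many workers answer the questionnaire, the error in that contrast includes the ordinary variation between departments. After school and arm are accounted for, four departments leave one degree of freedom to estimate that variation. A likelihood fit will often put it at zero. A normal-theory test then treats the arm effect as if it rested on several hundred independent workers.

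At stake are the claims on both primary outcomes: an ordinary difference between two pairs of departments could be reported as a significant intervention effect. Such differences are plausible here. The Methods/Design section says that the schools chose the intervention departments because of a problem or goal in a specific department.

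**Working it through.** **Inputs from the protocol article.** Two schools, four departments, two-sided alpha 0.05. Workers per department m = 97, from Sample size: 193 per arm / 2 schools = 96.5, rounded up.

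**Assumptions.** The ICC is not in the article, so it is varied from 0 to 0.05. The Wald test (|z| > 1.96) is inferred from the naming of multilevel analyses in MLwiN.

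**Arm effect.** Let D1 and D2 be the intervention-minus-control differences in the two schools. The estimate is (D1 + D2)/2. Each school holds both arms, so school effects cancel. With total variance 1, department variance = ICC and worker variance = 1 − ICC:

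- True variance of the estimate = ICC + (1 − ICC)/97.
- The only information on department variation around the arm effect is (D1 − D2)²/4. It has that same expectation, on 1 df.

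**Single-level regression.** It uses about (1 − ICC)/97, so the true variance is larger by the factor 1 + 97·ICC/(1 − ICC). Type I error = 2(1 − Φ(1.96/√factor)). At ICC 0.02 the factor is 1 + 97 × 0.02/0.98 = 2.98, its root is 1.726, 1.96/1.726 = 1.135, and the error is 26%. At ICC 0 the factor is 1 and the nominal 5% is recovered.

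**Three-level model as listed (school random).** 400,000 null trials were simulated per ICC. The balanced model was solved exactly with non-negative variance components, and the arm effect was tested at 1.96.

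**Valid reference.** With the school pair as block, the test is a t on 1 df, with critical value 12.71 instead of 1.96. Power for d = 0.2 comes from the noncentral t with noncentrality 0.2/√(ICC + (1 − ICC)/97).

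| ICC | Wald, REML | Wald, ML | Single-level | Power, 1-df t |
|---|---|---|---|---|
| 0 | 4% | 5% | 5% | 12% |
| 0.005 | 8% | 10% | 11% | 10% |
| 0.01 | 11% | 14% | 16% | 9% |
| 0.02 | 16% | 21% | 26% | 8% |
| 0.05 | 23% | 30% | 43% | 7% |

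The 1-df test holds 5.0% at every ICC.

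**Further results.**

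- At ICC 0.02 the department variance is estimated as (near) zero in 47% (REML) or 64% (ML) of trials.
- The median model standard error is 74% / 72% (REML / ML) of the true one at ICC 0.01, and 61% / 44% at 0.05.
- More workers do not help: with 150 per department and ICC 0.02, the rates rise to 19.4% / 24.8%.
- With school fixed instead of random, the rates are about 10% / 15% at ICC 0.01, 15% / 23% at 0.02 and 21% / 34% at 0.05. Fixing school does not remove the inflation.
- A rough cross-check with a general mixed-model routine (about 300 fits per setting, many not converging) gave 12% at ICC 0.02 and 17-21% at 0.05: lower, but in the same direction.

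**The case against.** **The inflation is conditional.** It needs a non-zero department ICC, and the article gives none. At ICC 0 the Wald test is correct or slightly conservative. A separate analysis plan might also specify a small-sample correction. Both points stand, so a reader who infers that the standard errors are certainly too small goes beyond the documents. Neither removes the concern: a later plan can change the test but cannot add departments, and with 1 df a valid correction leaves almost no power.

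**The missing occasion level.** Because repeated measurements are said to be handled while worker is the lowest level listed, a reader might infer that a worker's T1 and T2 records are treated as independent. The article does not support that. It speaks of effects at each follow-up corrected for baseline, and of "Multilevel analyses wherein T1 functions as the dependent variable, will be adjusted for possible confounding factors". That reads as one baseline-adjusted model per follow-up, in which worker is rightly the lowest level and no inflation arises from this source. Only a stacked T1/T2 analysis without a worker effect would understate the error, and no section describes one. This is a point to clarify.

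**The SPSS regressions.** A reader might infer that the effect claim will rest on them. The article says effectiveness will be established by multilevel analyses and does not give the purpose of the regressions. The single-level rates matter only if such a regression is used to test the arm effect.

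**The two schools.** A school variance from two units is poorly estimated, but school cancels from the arm contrast. The department level does the damage.

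**Disclosure.** The Discussion acknowledges the quasi-experimental design and possible selection bias. It does not mention the small number of departments.

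**Conclusion.** The concern holds in conditional form. Two schools and four departments cannot supply a department variance on which to base a test at p < 0.05. With an uncorrected Wald test and 97 workers per department, the false-positive rate is 4-5% at ICC 0, already 8-10% at 0.005, and 11-30% for ICCs from 0.01 to 0.05. A single-level test of the arm effect would run from 5% to 43% over ICC 0 to 0.05. These figures rest on the assumed ICC range, the inferred Wald test and balanced departments. The conclusion that the arm effect has about 1 df follows from the design alone. A valid 1-df test has only about 7-12% power for d = 0.2. The limit therefore lies in the design, and no choice of model makes a significant result attributable to the intervention rather than to department differences.

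**What to change.** 1. Fit school as a fixed block, since the departments are matched within school. This tidies the model but does not by itself remove the inflation.
2. Do not rely on the department variance estimated from four units. Report the arm effect and its confidence interval over a stated ICC range that includes 0, for example 0, 0.005, 0.01, 0.02 and 0.05.
3. Show the intervention-control difference for each school separately.
4. Label any single-level SPSS regression of the arm effect as descriptive.
5. State that p < 0.05 cannot separate the intervention from department differences, giving the 1-df reference (critical value 12.71, power about 7-12% for d = 0.2).
6. Say whether T1 and T2 are modelled separately or jointly. If jointly, make occasion level 1 within worker.

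The work is a change of wording and a few extra runs. The real cost is much wider intervals and a weaker confirmatory claim. Before baseline adjustment, the 95% half-width is 1.96 × √(ICC + (1 − ICC)/97): 1.96 × 0.1015 = 0.20 SD at ICC 0, 1.96 × 0.1735 = 0.34 SD at 0.02 and 1.96 × 0.2445 = 0.48 SD at 0.05, against a target effect of 0.2 SD.

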## Methods/Design

A quasi-experimental field study is conducted to determine the effectiveness of the participatory action approach (phase 1: needs assessment) and tailored work-oriented solutions (phase 2: implementation plan), compared to business as usual. The study is designed as a controlled trial (CT) with mixed methods (quantitative and qualitative) and three measurement moments: T0 at baseline (quantitative measurement), T1 at six months (quantitative and qualitative measurement) and T2 at 18 months (quantitative and qualitative measurement) (Figure 2). A CT is necessary to control for random changes, although the researchers are well aware of the fact that they are conducting a *social* experiment and that causal relations are thus embedded in complex contexts [38]. Randomization to experimental group (intervention group) or control group is practically impossible in this project, as often in organizational level workplace interventions [38], due to the aspirations of participating schools. Both schools participate in the study because they aim to solve a problem or reach a goal within a specific department of the school. The experimental groups were thus selected by the schools. To reduce the negative impact of selection bias, the control groups are selected by the researchers according to the ‘general control’ matching principle (or: frequency distribution control) [48]. Matching criteria are: department size (at least 150 employees), mean age of employees, and type of work (i.e. teaching vocational students and not secondary school pupils). Since the assignment to groups was out of our control, we will examine in the analyses whether propensity score matching is necessary. By applying the statistical technique of propensity score matching, the effect of the intervention can be estimated accounted for covariates that predict receiving the intervention. This way we expect to nullify potential confounding bias [49].

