##### Step 1: In-depth interviews

The Engine of Development approaches some prominent colleagues for an in-depth, open interview with the HM-facilitator. Prominent colleagues can be the typical optimists, pessimists, innovators, integrators or otherwise interesting employees that help the HM-facilitator grasp both initial hindrances to happy and healthy working as well as implicit norms in the intervention group. Approximately ten interviews will be held, or until saturation is reached. The HM-facilitator writes a report on his findings that is sent to all employees, after consulting the Engine of Development and the management team, respectively.

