##### Step 2: Digital, open ended questionnaire

Based on the report of the in-depth interviews, the Engine of Development compose the questions for a digital, open ended questionnaire. The open ended questionnaire should further specify the hindrances that were found in the in-depth interviews. All employees in the intervention group are invited to take part in the questionnaire. The HM-facilitator writes a report on the findings that is sent to all employees, after consulting the Engine of Development and the management team, respectively.

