##### Step 3: Group sessions

Based on the report of the open ended questionnaire, the Engine of Development determines several clusters of hindrances that need to be specified further in group sessions. The aim of the group sessions is not only to specify hindrances, but also to propose work-oriented solutions. All employees in the intervention group are invited to take part in the group sessions, which are chaired by the Engine of Development (except for the researcher). To ensure ‘freedom of speech’, the management team and staff have their own group sessions.

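### The supplementary per-protocol analysis sets self-selected attenders against controls who have no attendance to select on, and none of the stated adjustments is aimed at that selection

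*Protocol article*

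**What the plan says.** All references are to the Protocol article.

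- **Status of the analyses (Effect evaluation).** "The intention-to-treat principle is leading in all statistical analyses". The text then adds: "However, per-protocol analysis will also be conducted, restricting the comparison to the ideal participants". These are defined as "participants that report taking part in at least two of the three steps of the needs assessment". No corresponding rule is given for the control group.
- **Access to the three steps (The intervention, phase 1).** For step 1, "The Engine of Development approaches some prominent colleagues for an in-depth, open interview with the HM-facilitator", and "Approximately ten interviews will be held, or until saturation is reached". For step 2, "All employees in the intervention group are invited to take part in the questionnaire". For step 3, "All employees in the intervention group are invited to take part in the group sessions".
- **Controls (Study population; Methods/Design).** Controls work in another department of the same school under business as usual. "Matching criteria are: department size (at least 150 employees), mean age of employees, and type of work".
- **Adjustment (Effect evaluation; Methods/Design).** Effects are corrected for baseline values. Crude and adjusted models are both planned, and the T1 models are adjusted for confounders, with experience and overtime as examples. Propensity score matching will be used if judged necessary; the reason given is that the researchers did not control assignment to groups.
- **Where attendance is recorded (Process evaluation, Table 1).** Dose received comes from the T1 questionnaire and the facilitator's logs.

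**The concern.** A per-protocol comparison is informative only if the people kept in one group have a comparable counterpart in the other. Here membership depends on an employee's own choice to fill in an open-ended questionnaire and come to a session. Controls are offered neither. Applied literally to both groups, the rule leaves no controls, so the workable reading is attenders against unrestricted controls.

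That choice may be related to the outcome. The article itself describes vital workers as willing to put effort into their work, and it reports strong scepticism towards surveys in schools, so completers are unlikely to be a neutral subset. If attenders would have changed differently from non-attenders without any intervention, the per-protocol estimate mixes that difference with the intervention effect. The same 0.05 threshold applies to all analyses, and nothing marks this one as exploratory.

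A smaller point is that the rule asks different things of different people. An interviewee qualifies with one further step, while everyone else must complete both open steps.

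**Working it through.** The article attaches no figure to the per-protocol set, so there is none to reproduce.

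**1. Who can take step 1.** Reading the ten interviews as per intervention department:

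- 10 / 150 = 6.7% of a department at the minimum size, and less in a larger one
- 10 / 97 = 10.3% of the analysable number per group per school (Sample size)

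So about 90% to 93% or more of staff can take only steps 2 and 3. For them, two of three means both of two.

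**2. Size of the selection bias when the true effect is zero.**

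From the article: 193 analysable per group, design effect d = 0.2, two-sided 0.05, baseline correction.

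Assumed, because the article gives no values:

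- share p of intervention staff meeting the rule: 30%, 50%, 70%
- correlation r between attendance propensity and the part of the outcome not explained by baseline: 0 to 0.3
- baseline to follow-up correlation ρ = 0.6
- no clustering

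The approximate bias, in SDs of the outcome, is

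bias = r × φ(z) / p × √(1 − ρ²), where z is the (1 − p) normal quantile.

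- φ(z)/p is 1.159 at p = 0.3, 0.798 at p = 0.5 and 0.497 at p = 0.7.
- √(1 − 0.36) = 0.8 converts residual SDs to outcome SDs, the scale of d = 0.2.
- Example: r = 0.2, p = 0.3 gives 0.2 × 1.159 × 0.8 = 0.185.

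A simulation of the baseline-adjusted model compared attenders with all 193 controls (4,000 runs per cell, attendance also correlated 0.3 with baseline). Its results are close to the formula:

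| r | p = 30%: bias (type I error) | p = 50% | p = 70% |
|---|---|---|---|
| 0 | 0.00 (5%) | 0.00 (5%) | 0.01 (5%) |
| 0.1 | 0.09 (12%) | 0.07 (10%) | 0.04 (8%) |
| 0.2 | 0.19 (33%) | 0.13 (24%) | 0.08 (15%) |
| 0.3 | 0.28 (64%) | 0.20 (50%) | 0.12 (27%) |

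The r = 0 row shows that baseline correction works when attendance depends only on the baseline outcome. The other rows show what it leaves behind. A negative r gives the same sizes with the opposite sign.

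**3. Do the stated safeguards address attendance?** Baseline correction removes selection through the baseline score. Adjustment for named confounders removes selection through those variables. Propensity matching, if used, models which department received the intervention, not who within it attended. None is directed at attendance given baseline.

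**The case against.** **Intention-to-treat leads.** This stands. The per-protocol analysis is additional, and nothing here touches the main result. Self-selection of attenders is also a familiar limit of such analyses.

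**The comparator may be in the full protocol.** This stands in part. That the comparator is unnamed in a condensed article is not in itself an error, and unrestricted controls are an inference. But the rule that is printed depends on attendance, and no attendance rule can be applied to people who were offered no steps.

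**The comparison is adjusted.** This also stands. A reader might infer an unadjusted contrast, but the article plans baseline correction and confounder adjustment. The concern is confined to selection beyond those variables.

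**The step 1 unevenness hardly matters.** Correct. A reader might take it as the main flaw, but it can change the classification only of interviewees who missed one open step, at most about ten per department.

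**The direction is unknown.** A reader might infer that the bias must favour the intervention. The text does not support that: the steps collect hindrances, and typical pessimists are among those who may be interviewed, so strained staff could be drawn in as readily as energetic staff.

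**Phase 2.** A reader might infer that the same set will serve as the per-protocol population for the implemented solutions at T2. The article does not say so, and T2 is also meant to show long-term effects of taking part in the needs assessment. What remains is a labelling point: attendance in phase 1 does not measure exposure to phase 2.

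**Conclusion.** The point holds for the supplementary per-protocol analysis only. As worded, that analysis would compare self-selected attenders with controls on whom no matching selection can act, and the adjustments described do not target attendance.

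Under the assumed attendance of 30% to 70% and residual correlation of 0.1 to 0.3, the bias is about 0.04 to 0.28 SD, with a false-positive rate of about 8% to 64% in place of 5%. The upper part of that range reaches or exceeds the 0.2 SD the trial is designed to detect. If attendance depends only on baseline values the bias is about zero. Attendance, residual correlation and baseline correlation are all assumed, so the table shows what is possible and does not predict what will happen. The unevenness from step 1 is minor.

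**What to change.** 1. Define adherence on the two steps open to everyone, the questionnaire and the group session, and record the interview separately.
2. Name the control comparator, and weight or match controls to attenders on T0 variables: baseline outcome, occupational self-efficacy, commitment, age and school. Add teaching or support role if it is recorded; the article's list of sociodemographic items does not name it.
3. Label the result exploratory, as an effect of taking part in phase 1 and not of the phase 2 solutions.

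A complier-average estimate with department as the instrument is not a suitable substitute. The schools chose the intervention departments, and non-attenders also receive the reports and the plan of action and work under whatever is implemented.

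The cost is a few lines of wording, a modest extra analysis on planned data, and some loss of precision from weighting. Weighting cannot remove selection on unmeasured motivation, so the exploratory label is needed even after it.
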